#### Data forms

A combination of standardized paper-based or digital forms (under Android tablets) will be used. MRTC, CRS, and University of Notre Dame (UND)/Center for Research Computing (CRC) will work together to develop the quantitative forms to be uploaded on Android phones. Entered data (entomological and epidemiological) will be automatically assessed for quality using established quality control rules, then reviewed and appended to the data already present. Data forms can be made available upon request submitted to UND. Any changes to the forms will need to be agreed by the cRCT overall CRS PI (in consultation with CRS’ technical advisors), the country level MRTC and CRS PIs, and UND’s co-PI. In the event a consensus on proposed changes cannot be achieved, UND’s PI will make the final decision.

### Plans to promote participant retention and complete follow-up {18b}

Participant retention strategies will include study staff directly visiting study participants in their HHs twice a month. Additional strategies will include participant tracing when they miss appointments, visit reminders, request participants to inform study staff of moves outside or within the study area, foster relationships with participants as they engage in ancillary care at study clinics, provision of Clinical Officer’s contact information for easy communication to alleviate any concerns, and periodic generation of retention rate to evaluate strategies. A study SOP will be developed to provide more details on retention activities to be conducted by study staff.

### Data management {19}

#### Data forms

A combination of standardized paper-based or digital forms (under Android tablets) will be used so variable codes can be cross-referenced during the final analysis. All data issuing from the electronic data collection system will follow the same data collection processes outlined in the paragraph below.

#### Data quality control and quality assurance

Data management study staff will be responsible for verifying data accuracy and assuring data collection is following standardized protocols. These activities will promote data quality and ensure the trial is performed in compliance with GCP and the applicable regulatory requirements(s). Training on data collection will occur prior to the start of baseline and throughout the trial period with refresher trainings. Standardized data collection forms will be used and source data verification will occur through three primary mechanisms: (1) Self-quality checks, making sure data forms are fully completed; (2) Data queries, quality checks on a routine basis; (3) External monitoring, by fhiClinical, the clinical research organization responsible for trial oversight. In addition, tablet-based digital forms which will be used for data entry will be custom designed to include rules and conditions for data variable responses (e.g., text responses cannot occur for a numeric value, and thresholds for numeric data).

#### Data sharing policy

Using CommCare, the study teams will collect data which will be securely stored on Android devices and synchronized to the CommCare cloud. Data will undergo an initial cleaning and de-identification by the study team, before being synced to UND’s central database. Data from MRTC to UND will be transferred through a dedicated secure FTP server with password-protected access from MRTC and CRS.

This project will generate considerable data and biological samples over the course of the 2-year study period. The data management plan will follow the guidelines and suggestions put forward by the National Institutes of Health in its online guidance document https://humansubjects.nih.gov/data_safety and by the respective institutions involved in the research (MRTC, UND, and CRS), as well as by the community of interest (comprised of colleagues, scientists working in the same field, the biomedical community researching tropical parasitic diseases, and public health officials). The goal is transparent sharing of key findings and data so that the broad impacts of the research are meaningful and useful to key stakeholders and will therefore be shared with stakeholders as may be required.

Every consideration will be given to the nature of beneficence and justice expressed in the guiding documents for research on human subjects. Biological samples of mosquitoes and parasites will be maintained appropriately to avoid deterioration. These materials will be made available to researchers upon reasonable request and with the caveat that any forthcoming publications from research on the samples should consider the original researchers and their inclusion in the resulting publications when warranted.

#### Data storage

Any data collected with paper forms (including consent forms) will be scanned and transferred to binders for storage in a secure and locked restricted access area, while all electronic captured data will be archived with a documented history of changes or corrections at the local study site. Using CommCare, MRTC (with technical support from CRS) will collect data which will be securely stored on Android devices and then synchronized to CommCare cloud at least every 14 days. MRTC will download the data from CommCare and conduct initial data cleaning and de-identification, in collaboration with CRS, before syncing it to UND’s central study database. The downloaded data will be stored on password-protected computers at the MRTC office to ensure confidentiality. Data from MRTC to UND will be transferred through a dedicated secure sFTP server with password protect access from MRTC via CommCare.

A password-protected central study database warehousing data from all sites will be developed and managed by UND and serve as a data repository and utilized for safe and confidential data storage, extraction, integration and analysis. The data warehouse and file repository will be backed up weekly at the local server level to ease recovery as needed. In addition, data is stored and backed up on CommCare cloud. Access to study data will be controlled through centralized administration and access will be granted only through the PI’s permission. Research records for all study subjects including history and physical findings, and results of consultations are to be maintained by the local site PI in a secure storage facility and by UND and CRS, for a minimum of 3 years after the end of the projects per national guidance or until notified by grantee. Data and samples can be destroyed at any given time after those 3 years.

### Confidentiality {27}

Any participant information will be confidential and will not be given to anyone who is not sensitive to the participant’s health. The results of this study will be made publicly available to sponsors of this study but personal information will not be provided to anyone.

The UND CRC will not share identifiers, but instead, use a code. The code will be kept by the UND CRC, and securely at the MRTC site according to site-specific IRB specifications and requirements for emergency situations. Raw data will be anonymized and GPS tag-blurred to remove sensitive information prior to sharing to other study sites or outside of the core study team according to local IRB requirements.

Participant privacy/confidentiality protection will be assessed during routine quality assurance activities and based on the SOPs developed for the project. A set of protocols and contingency plans for emergency paper-based and digital data destruction will be developed in order to guarantee privacy of research subjects in case of unforeseen risks.

### Plans for collection, laboratory evaluation, and storage of biological specimens for genetic or molecular analysis in this trial/future use {33}

This study does not include genetic or molecular analyses. Standardized protocols will be developed for the collection, storage, use, and post-trial destruction of blood samples collected as part of the trial.

## Statistical methods

### Statistical methods for primary and secondary outcomes {20a}

#### Primary hypothesis

H_0_: SR does not reduce the first-time malaria hazard rate compared to placebo in Mali.

H_1_: SR reduces the first-time malaria hazard rate compared to placebo (overall malaria hazard ratio between SR and placebo is <1; the expected hazard ratio is 70% or PE is 30%).

#### Secondary hypothesis

H_0_: SR does not reduce the overall malaria hazard rate compared to placebo in Mali.

H_1_: SR reduces the overall malaria hazard rate compared to placebo (overall malaria hazard ratio between SR and placebo is <1; the expected hazard ratio is 70% or PE is 30%).

#### Population for analysis

The intention to treat (ITT) analysis is the primary analysis approach for both the primary and secondary objectives. The ITT population includes the first recruited child from each recruited HH that receives at least one SR product or placebo per the cluster randomization schedule. If a recruited subject comes from a HH used for entomological data collection, that subject will be not used in the ITT analysis. The per-protocol (PP) analysis is included as a supplementary analysis for the primary and secondary objectives. The PP population includes the subjects from the ITT population that are treated following the specifications of the study protocol without major protocol deviations.

#### Statistical methods—primary endpoint (ITT population)

The baseline characteristics of the enrolled subjects, HHs, and clusters will be summarized by treatment arm. Specifically, we will examine subject age and gender at the individual level, wall type and roof type, floor height, house open eaves, # of window, # of doors at the HH levels, and cluster population and baseline overall infection incidence at the cluster level.

The primary hypothesis on PE against the first-time malaria infection will be tested by comparing the hazard rates of first-time malaria infection between SR and placebo upon the completion of the study in the ITT population via a cloglog regression for the interval-censored time to event data. The model will include the treatment arm (SR vs. placebo), relevant baseline covariates, and a random effect that accounts for the dependency among data collected from the same cluster. PE against the first-time infection is estimated by ($$ 1-\exp\ \left(\hat{\beta}\right)\ \Big)\times $$100%, where$$ \hat{\beta} $$ is the estimated regression coefficient associated with the treatment group, with a 90% 2-sided confidence Interval (CI) based on the Wald test. The lower bound of the 90% CI corresponds to the lower bound of the 95% 1-sided CI (the hypothesis is one-sided).

#### Statistical methods—secondary endpoints

##### PE of SR against the overall (both first-time and recurrent) malaria infection

The secondary hypothesis on PE against the overall new malaria infections will be tested by comparing the hazard rates of the overall malaria infection between SR and placebo in the ITT population. using a similar approach as for the first-time infection with an additional random effect term to account for the dependency among the multiple malaria incidences collected from the same individual. PE against the overall infections is estimated by ($$ 1-\mathit{\exp}\ \left(\hat{\beta}\right)\ \Big)\times $$100%, where$$ \hat{\beta} $$ is the estimated regression coefficient associated with the treatment group, with a 90% 2-sided CI based on the Wald test. The lower bound of the 90% CI corresponds to the lower bound of the 95% 1-sided CI (the hypothesis is one-sided).

##### Subgroup PE analysis by age group

The above analysis of the first-time and overall malaria infections in the examination of the PE of SR will be based on all the subjects aged: ≥6 months to < 10 years. The same set of analysis will also be performed by two age subgroups: ≥6 months to 59 months old and 6 to < 10 years old to examine if the PE of SR will differ by two age groups.

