### Eligibility criteria {10}

The inclusion and exclusion criteria are listed in Table 1 below. Children aged ≥6 months to < 10 years of age who report sleeping in selected study clusters > 90% of the nights of each month and do not have any plans to travel outside the study area will be eligible for inclusion in the study. Children who have a measured hemoglobin at baseline screening/enrollment, re-screening/re-enrollment for intervention phase of < 7 g/dL, or with known chronic disease or who have signs of clinical decompensation will also be excluded from the study. During follow-up of enrolled subjects, study clinicians will have the option to conduct a Hb test for enrolled subjects when they may present signs of anemia to see if they might need additional treatment beyond malaria ACTs (if malaria infection is indicated).

**Table 1 Tab1:** Inclusion and exclusion study criteria

Inclusion criteria	Exclusion criteria
Children ≥ 6 months to < 10 years of age	Children ≤ 6 months to > 10 years of age
Children with Hb ≥ 7 g/dL and no other serious illness	Children with Hb < 7 g/dL with signs of known chronic disease or other serious illness, or Hb < 6 g/dL with signs of clinical decompensation
Sleeps in cluster > 90% of nights during any given month	Sleeps in cluster < 90% of nights during any given month
Not participating in another clinical trial investigating a vaccine, drug, medical device, or a medical procedure during the trial	Participating or planned participation in another clinical trial investigating a vaccine, drug, medical device, or a medical procedure during the trial
Provision of informed consent form (ICF) signed by the parent(s) or guardian	No provision of ICF signed by the parent(s) or guardian

Persons who are participating in another clinical trial investigating a drug, vaccine, medical device, or procedure will also be excluded from the study. The written consent of the parent or legal guardian of each child will be required for inclusion in the study.

For those participants fitting the study criteria, trained study personnel will be employed to ensure the timely distribution, application, and replacement of the SR products and to perform periodic, unannounced spot checks to confirm the SR product is properly installed.

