### Outcomes {12}

The primary outcome measure of this cRCT will be the number of first-time malaria infections (*Plasmodium falciparum* (Pf)) during the intervention period (24 months) as measured by microscopy in children aged between 6 months and 10 years.

Secondary outcome measures include:
2.Number of overall new *Plasmodium falciparum* malaria infections during the intervention period (24 months) as measured by microscopy in children aged between 6 months and 10 years;3.Number of first-time *Plasmodium falciparum* malaria infections during the intervention period (24 months) by two age groups (≤ 6–59 months old; 5–10 years old) as measured by microscopy in children aged between 6 months and 10 years;4.Number of overall *Plasmodium falciparum* malaria infections during the intervention period (24 months) by two age groups (≤ 6–59 months old; 5 years to 10 years old) as measured by microscopy in children aged between 6 months and 10 years;5.Anopheline-human contact (indoor and outdoor) using human biting rate (HBR) as an indicator for all anophelines and by anopheline species as measured by human landing catch (HLC) during 12-h intervals on a quarterly basis during the intervention period (24 months);6.Anopheline parity rate as an indicator of population age structure for all anophelines and by anopheline species as measured by mosquito ovarian dissections from a sub-sample of anophelines collected during HLC procedures during the intervention period (24 months);7.Anopheline infectivity using sporozoite rate as an indicator for all anophelines and by anopheline species as measured by laboratory detection of sporozoites in mosquito head-preps from a sub-sample of anophelines collected during HLC and/or CDC-light trap procedures during intervention period (24 months);8.Anopheline infectivity using entomological inoculation rate (EIR) during the intervention period (24 months) as an indicator for all anophelines and by anopheline species as measured by calculating the number of sporozoite-infected anopheline mosquitoes captured per person during intervention period from HLC and/or CDC-light trap procedures;9.CDC-light trap indoor density for all anophelines and by anopheline species as measured by CDC-light trap collections during 12-h intervals on a monthly basis during the intervention period (24 months);10.Insecticide resistance as measured by WHO filter paper test and CDC bottle assays during the baseline (6 months) and intervention period (24 months);11.Adverse events (AEs) and serious adverse events (SAEs) as measured by solicited and unsolicited reports during baseline (6 months) and intervention period (24 months). Mean, minimum and maximum frequency, and percentage of AEs and SAEs across clusters among enrolled subjects will be summarized by the treatment arm.

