#### Primary hypothesis on first-time malaria infection

The sample size determination on the required number of subjects (HHs) per cluster for testing the primary hypothesis on PE is based on the hazard rate comparison in the proportional hazards regression model [7, 8]. With the following specifications: 1-sided type-I error rate = 5% (because the primary hypothesis is one-sided as SR is very unlikely to increase the hazard rate of malaria infection compared to placebo), true PE = 30%, a between-cluster coefficient of variance (CV) of hazard rate = 47% (based on the historical data collected from Mali) then 788 independent first-time malaria events will need to be observed to reach 80% power in testing the primary hypothesis on PE.

With a baseline first-time malaria infection hazard rate of 1.0 per person-year (ppy), 30 clusters per treatment, 26 subjects (HHs) per cluster (factoring in a LTFU rate at 35%) in each treatment arm post randomization are expected to yield 788 independent first-time malaria events within 24 months follow-up period per cohort post randomization to yield 80% power. If, by the end of the 2-year study, 788 independent malaria events are not reached, the study may extend until 788 events are collected without inflating the type I error rate in the testing of the primary hypothesis. The same number of HHs (26) will be recruited into the baseline period. It is expected that 80% of the baseline HHs will continue to participate in the intervention period.

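### The age-subgroup analysis starts its older group at 6 years while the matching outcomes start it at 5, so read literally 5-year-olds fall in neither group

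*Protocol article*

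**What the plan says.** Three parts of the protocol article bear on this.

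- **Analysis.** The section Subgroup PE analysis by age group first says that the first-time and overall infection analyses "will be based on all the subjects aged: ≥6 months to < 10 years". It then repeats them in two subgroups, "≥6 months to 59 months old and 6 to < 10 years old". The purpose given for this repetition is "to examine if the PE of SR will differ by two age groups".
- **Outcomes.** Outcomes {12} declares the matching secondary outcomes. Item 3 (first-time infections) uses "≤ 6–59 months old; 5–10 years old". Item 4 (overall infections) uses "≤ 6–59 months old; 5 years to 10 years old". Both start the older group at 5 years.
- **Eligibility.** Eligibility criteria {10} admits "Children aged ≥6 months to < 10 years of age who report sleeping in selected study clusters > 90% of the nights of each month". Five-year-olds are inside that range, and no section excludes them from the subgroup analysis.

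For season and year, the section Temporality of PE effects adds each factor and its interaction with the intervention to the cloglog models. The age-subgroup section mentions no interaction.

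**The concern.** The two sections describe the same analysis with different cut-points. In completed months, 59 runs up to the day before the fifth birthday. An older group that starts at 6 years therefore leaves a full year of age unassigned.

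Two declared secondary outcomes are at stake. A programmer working from the methods text would report the subgroup results on part of the cohort, and the two subgroups would not add up to the total. A programmer working from the outcome list would include everyone. If nobody settles which applies before unblinding, the cut-point becomes a choice that can be made with the results in view.

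The second, smaller issue is that the stated aim is to learn whether efficacy differs by age, but the text as worded only repeats the analysis within each group. Two efficacy estimates, each with its own interval, do not give an estimate of their difference. Nor can a reader safely recover one from the two intervals. Randomisation is by cluster, so both age groups come from the same clusters and their treatment estimates need not be independent.

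**Working it through.** The protocol states no figure for the subgroup sizes, so there is none to reproduce. The check assigns every eligible completed month of age to a group under each definition.

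**Inputs**

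- Eligible ages, ≥6 months to <10 years: completed months 6 to 119, so 119 − 6 + 1 = 114 monthly ages (Eligibility criteria {10}).
- Younger group, the same in both sections at its upper end: months 6 to 59, so 59 − 6 + 1 = 54.
- Older group in the analysis section, from 6 years: months 72 to 119, so 119 − 72 + 1 = 48.
- Older group in Outcomes {12}, from 5 years: months 60 to 119, so 119 − 60 + 1 = 60.
- Intervention-phase cohort: "30 clusters per treatment, 26 subjects (HHs) per cluster (factoring in a LTFU rate at 35%) in each treatment arm post randomization" gives 2 × 30 × 26 = 1560 children, one per household.

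**Coverage of the eligible ages**

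| Definition | Younger | Older | Total | Unassigned |
|---|---|---|---|---|
| Analysis section | 54 | 48 | 102 | 114 − 102 = 12 (months 60 to 71) |
| Outcomes {12} | 54 | 60 | 114 | 0 |

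**Size of the gap in months of age**

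- Share of the eligible span: 12 / 114 = 10.5%.
- Share of the older group as the outcomes define it: 12 / 60 = 20%.

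**Size of the gap in children**

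The article gives no age distribution, so the share of children aged 5 is an assumption.

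| Assumed share aged 5 | Children in neither group, of 1560 |
|---|---|
| 8% | 0.08 × 1560 ≈ 125 |
| 10.5% (uniform ages, 12/114) | 12/114 × 1560 ≈ 164 |
| 13% | 0.13 × 1560 ≈ 203 |

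**The comparison between age groups.** Temporality of PE effects and the age-subgroup section ask the same kind of question, namely whether efficacy varies across levels of a factor. The first answers it with a term for the factor's interaction with the intervention. The second, as worded, stops at separate results by level. The model already planned can carry the age term in the same way.

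**The case against.** The strongest reply is that this is a one-digit slip. Outcomes {12} gives the 5-year boundary twice, 59 months pairs naturally with 5 years, and the analysis section itself presents its groups as a split of the full age range. That stands. A reader might infer that 5-year-olds are deliberately dropped, or are certain to be lost from the results. The article supports neither; the loss occurs only if the analysis text is followed literally. The reply does not remove the point, because that section is the one that specifies the analysis, and it contradicts the outcomes it serves.

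A second reply is that the article does not rule out an interaction term, and that the way a subgroup contrast is estimated is commonly left to a statistical analysis plan, which is not shown here. This has weight, and the interaction is therefore offered as an inexpensive improvement that matches what the article does for season and year. It is not a claim that the planned subgroup fits are invalid. Nor does the article state any rule for declaring an age difference, so a false claim of one cannot be read into it.

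Two further inferences are tempting:

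- **Seasonal chemoprevention as the reason for the split.** The article says that chemoprevention covers children of 3 to 59 months, so the unassigned year lies just above that limit. No section says that this motivated the age groups.
- **A count of lost infections.** This would need the age distribution and age-specific hazards, and the article gives neither. Equal hazards on both sides of the chemoprevention limit cannot simply be assumed.

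**Conclusion.** The contradiction is real and confined to the age-group secondary outcomes, items 3 and 4. The primary analysis of first-time infection and the all-age analysis of overall infection use every eligible age and are not touched.

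In months of age the size follows directly from the text and needs no assumption: 10.5% of the eligible span, and one fifth of the older group. The counts of 125 to 203 children, with 164 under uniform ages, are illustrative. They rest on an assumed 8% to 13% of children being aged 5 and on the planned 1560.

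This should be corrected: it affects two declared outcomes, the intended boundary is evident, and the repair is small. The absence of a stated interaction is a lesser matter of matching the analysis to its own aim.

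**What to change.** 1. **Boundary.** State the groups identically in Outcomes {12} and in Subgroup PE analysis by age group: ≥6 to 59 months, and 60 months to <10 years. Correct the ≤ sign before the 6 in the outcome list at the same time. This costs wording only.

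2. **Age reference.** Say that age is taken at intervention enrolment. Follow-up lasts 24 months, so a child enrolled at 54 months would be 54 + 24 = 78 months at the end and would cross the boundary on the way. Fixing age at enrolment keeps each child in one group. This costs one sentence.

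3. **Interaction.** Add a treatment-by-age-group interaction to the cloglog models for first-time and overall infection, as is already planned for season and year. Report it with its confidence interval beside the two subgroup efficacies. This is more than a wording change, since it adds a model term. The contrast will have low power and should be labelled exploratory.

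All three should be settled before the biostatistician is unblinded. The article places that after database lock, so there is room to fix the cut-point without sight of results by arm.

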### Methods for additional analyses (e.g. subgroup analyses) {20b}

#### Temporality of PE effects

It is expected that malaria incidence changes by seasonality (rainy vs dry) and year. To examine the temporality of malaria incidence rates and the PE effect, a supplementary analysis will be performed by adding the seasonality (Jun–Dec/wet/peak and Jan–May/dry/low) and year (1 and 2) and their interaction with intervention to the covariate list in the cloglog models used for analyzing the first-time and overall infections. The PE will be estimated by seasonality and year.

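### The plan asks whether protective efficacy differs by age, but its only stated method tests each age group against no effect and never compares the two

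*Protocol article*

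**What the plan says.** Under the heading Subgroup PE analysis by age group, the protocol article gives a method, "The same set of analysis will also be performed by two age subgroups", and an aim, "to examine if the PE of SR will differ by two age groups". The analysis to be repeated is the one described for the primary endpoint and for overall infections. It is a complementary log-log model with treatment arm, baseline covariates and a cluster random effect, plus a subject random effect for overall infections. It yields a one-sided 5% Wald test of no reduction and a PE with a two-sided 90% confidence interval. No arm-by-age term or other comparison of the two PEs is stated.

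Elsewhere the document handles the same kind of question differently. Under Temporality of PE effects it adds season, year and "their interaction with intervention to the covariate list in the cloglog models used for analyzing the first-time and overall infections", and then estimates PE by season and year. Under Effects of SR on entomological endpoints, the biting-rate model contains an interaction between intervention and indoor or outdoor location.

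Infections by age group are listed secondary outcomes under Outcomes {12}. The age bands there do not match. Outcomes {12} starts the older band at five years, whereas the subgroup section ends the younger band at 59 months and starts the older one at six years, so five-year-olds fall in neither.

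**The concern.** The question is whether PE is equal in the two groups. The stated procedure tests PE = 0 twice, so it does not answer that question. If one result is significant and the other is not, the natural summary is that the product protects one age group only. That pattern can arise easily when efficacy is the same in both, because each subgroup test has less power than the whole-cohort test.

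An age difference is a reasonable thing to look for. According to the protocol, seasonal malaria chemoprevention covers children aged 3–59 months, so the younger band largely coincides with the children who receive it. A spurious difference, or a real one reported without a valid interval, would affect a listed secondary outcome. The primary hypothesis is not touched.

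**Working it through.** **Inputs.** From the section Primary hypothesis on first-time malaria infection: "1-sided type-I error rate = 5"%, true PE 30% (hazard ratio 0.70), "a between-cluster coefficient of variance (CV) of hazard rate = 47"%, 30 clusters per arm, a placebo hazard of 1.0 per person-year, and "788 independent first-time malaria events will need to be observed to reach 80% power". The age split of events is not given; 50:50 is assumed (394 each) and 30:70 is shown as well. How far the cluster effect is shared between younger and older children of the same village is not given either; fully shared, half shared and independent are shown.

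**Reproducing the plan's figure.** The Hayes–Bennett formula for rates, with y = 788 / (30 × 1.7) = 15.45 person-years per cluster, gives

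- z = √[30 × 0.3² / (1.7/15.45 + 0.47² × (1 + 0.7²))] − 1.645 = √(2.7 / 0.439) − 1.645 = 0.83, so power is 79.8%.

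Solving for exactly 80% gives 806 events, within 3% of 788. On the log hazard ratio scale, variance = 4/788 + 2 × 0.47²/30 = 0.0198, SE = 0.141 and power = 81.3%. The design is reproduced, and the log-scale form is used below.

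**Each subgroup, equal true PE of 30%.**

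- Variance = 4/394 + 2 × 0.47²/30 = 0.01015 + 0.01473 = 0.02488; SE = 0.158.
- Power = Φ(0.357/0.158 − 1.645) = 73%.

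**Chance that exactly one group is significant.** This is p₁ + p₂ − 2 × P(both), with P(both) from a bivariate normal distribution whose correlation is the shared part of 0.01473 divided by 0.02488.

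| Cluster effects between ages | Correlation | Exactly one significant, 50:50 | Exactly one significant, 30:70 |
|---|---|---|---|
| Fully shared | 0.59 | 24% | 28% |
| Half shared | 0.30 | 32% | 36% |
| Independent | 0 | 2 × 0.731 × 0.269 = 39% | 42% |

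A simulation of 400 trials (Poisson counts, lognormal cluster effects fully shared between ages, 50:50 split, no covariates) gave subgroup power of 73.0% and 73.5%, and exactly one group significant in 26%.

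**Precision of the difference.** In the same simulation the SD of the estimated difference in log hazard ratios was 0.153 from two separate fits and 0.151 from a joint model. Shared cluster noise cancels on subtraction in both cases. The standard errors do differ:

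- Two separate SEs combined as independent: √(2 × 0.02488) = 0.223 (simulated mean 0.219).
- Joint model, fully shared cluster effects: √(2 × 0.01015) = 0.142 (simulated mean 0.146).
- True SE if half shared: 0.187; if independent: 0.223.

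Under equal PE, a two-sided 10% test built on the combined separate SEs rejected in 1.25% of simulated trials; the joint interaction test rejected in 12.75%.

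**Power for a real difference, fully shared effects, two-sided 10%.** For PE 40% against 20%, log(0.8/0.6) = 0.288. Power is about 65% with SE 0.142 and about 36% with SE 0.223. For PE 30% against 15%, log(0.85/0.70) = 0.194, and Φ(0.194/0.142 − 1.645) is about 39% even with the joint model.

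**The case against.** The protocol nowhere says that the two significance results will be compared. It reports a PE with an interval for each group, so a reader could look at two estimates rather than two verdicts. Age-specific estimates are also the natural analysis of the listed age-group outcomes, and a contrast could be left to the analysis plan. The first part stands: the 24–39% is conditional on a reading that the text does not state. The last part does not, because the section does not defer the comparison. It names a method for examining a difference, and that method does not supply one, while season, year and location get an interaction in the same article.

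A reader might also infer that separate fits estimate the age difference with much lower precision or discard power. The documents do not support this. The point estimate of the difference is about equally precise either way. The gap between 0.223 and 0.142, and the power gap that follows from it, arises only if the two SEs are combined as independent, which no section proposes. It also requires cluster effects shared between ages, and it vanishes if they are independent.

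Finally, an interaction has limited power for modest differences, as the 39% figure shows. That argues for reporting an estimate with its interval, not for leaving out the comparison.

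**Conclusion.** The stated method does not answer the stated question: it tests no effect in each age group and gives no test or interval for a difference in PE. If the difference is read from which group is significant, equal efficacy of 30% would look like a difference in about 24–26% of trials with fully shared cluster effects, rising to about 39% with independent ones. These figures rest on the assumed 50:50 split of 788 events. Combining the two separate SEs instead would be too conservative to the extent that cluster effects are shared. Neither route is written in the protocol, and it offers no other.

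This concerns secondary analyses only; the primary test and the sample size are unaffected. It is worth correcting because the correction is cheap.

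**What to change.** 1. Reconcile the age bands in Outcomes {12} and in the subgroup section so that every enrolled child, including five-year-olds, belongs to exactly one group. A full-cohort age model cannot be specified until this is done.
2. For each endpoint, fit one full-cohort complementary log-log model with arm, age group, arm by age group, the planned covariates and the planned random effects. Add a cluster-by-age random term if it can be estimated; without it the SE of the contrast is understated when cluster effects differ by age.
3. Report the ratio of hazard ratios with a two-sided confidence interval, and make it the only basis for a statement that PE differs by age. Take both age-specific PEs with 90% intervals from this model. State that significance in one group but not in the other is not evidence of a difference.
4. The separate subgroup fits may stay as descriptive results.

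The cost is a paragraph of text and an added interaction per model, on data already being collected. The drawbacks are that covariate effects are shared across ages and that power for modest differences is limited, so the contrast should be presented as an estimate with its interval.
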